## Abstract

**Background:**

A cytotoxic chemotherapeutic regimen is not routinely recommended for frail elderly patients with unresectable colorectal cancer (CRC) because of susceptibility to treatment. Panitumumab is a monoclonal antibody targeting the epidermal growth factor receptor (EGFR). Use of panitumumab as first-line therapy is expected to be well tolerated and to improve survival rates, even in patients who are not eligible for intensive chemotherapy. However, the efficacy and safety of panitumumab as the first-line therapy for the frail elderly patients with unresectable CRC have not been yet studied.

**Methods:**

We plan to conduct a prospective multi-center phase II study. Patients with wild-type RAS unresectable CRC aged ≥76 years or ≥ 65 who are not considered eligible for intensive chemotherapy will be included in the study. A total of 36 patients will be enrolled from Osaka Gastrointestinal Cancer Chemotherapy Study Group for over 2 years. Panitumumab 6 mg/kg IV infusion will be administered every 2 weeks. The purpose of this trial is to assess the efficacy of panitumumab as first-line therapy for patients with unresectable CRC. The primary endpoint is to determine the disease control rate. Secondary endpoints include progression-free survival, overall survival, response rate, time to treatment failure, and the incidence of grade 3/4 toxicities.

**Discussion:**

This is a prospective phase II trial assessing the efficacy of panitumumab monotherapy in the elderly patients with wild-type RAS unresectable CRC.

**Trial registration:**

The ethics committee of the Osaka Medical College approved this study on November 7, 2016. The trial registration number of the government was UMIN000024528 on December 1, 2016. It was registered prospectively (the day of enrollment of the first participant was February 9, 2017).

## Background

Advanced colorectal cancer (CRC) is the second most common cause of death from cancer in the world, after lung cancer [1, 2]. The elderly patients constitute more than half of the CRC cases and their prevalence increasing continuously [3]. A similar tend is observed in Japan; CRC is the second most common cause of death from cancer, with more than half of patients aged > 75 years [4, 5].

Treatment strategies for advanced CRC have been developed over the last decades; consequently, the median overall survival (OS) has now reached 30 months [6]. However, the frail elderly patients have never been the subjects of the clinical trials investigating these treatment strategies [7]. A pivotal trial in frail patients with CRC demonstrated that single-agent fluoropyrimidines were favorable to progression-free survival (PFS) and resulted in a better quality of life than intensive chemotherapy that included oxaliplatin [8]. Furthermore, the combination of irinotecan and fluoropyrimidines did not show a significant improvement in PFS compared with fluoropyrimidines alone [9]. Thus, intensive chemotherapy should not be routinely recommended for the frail elderly patients with unresectable CRC. Combination therapy with 5-fluorouracil and bevacizumab has been demonstrated to be well tolerated and effective. In a phase III AVEX trial in elderly patients, a combination of bevacizumab and capecitabine was shown to be superior to capecitabine alone in improving PFS, the primary endpoint of the study [10]. Based on the AVEX trial, the combination of bevacizumab and capecitabine is considered a standard therapy for elderly patients with unresectable CRC. However, even single-agent fluoropyrimidines often have undesirable effects, including fatigue, anorexia, gastrointestinal toxicities, or hematologic toxicity. As is often the case with frail elderly patients, a cytotoxic regimen is not routinely recommended because of their susceptibility to treatment.

Panitumumab is an epidermal growth factor receptor (EGFR)-inhibiting monoclonal antibody. Use of panitumumab as first-line therapy is expected to be well tolerated and to improve the survival rates even in patients with wild type (WT) RAS CRC who are not considered eligible for intensive chemotherapy [11, 12]. The presence of WT RAS, including KRAS and NRAS*,* is predictive of the effectiveness of anti-EGFR monoclonal antibodies [13, 14]. Panitumumab-related toxicities, including skin toxicity or hypomagnesemia, require management; however, panitumumab treatment was rarely found to cause cytotoxicity, including fatigue, appetite loss, or neutropenia. Thus, panitumumab may be suitable for the frail elderly patients [11, 12]. In addition, panitumumab is administered every 2 weeks in contrast to cetuximab, another EGFR-inhibiting monoclonal antibody, which is administered weekly. In a phase II trial in Spain, Sastre et al. investigated panitumumab as first-line therapy in frail elderly patients (≥70-year, PS 0–2) with WT KRAS unresectable CRC [11]. The median OS and progression free survival (PFS) were 7.1 months (95% CI, 5.0–12.3) and 4.3 months (95% CI, 2.8–6.4), respectively. Pietrantonia et al. also reported a retrospective study on the efficacy and the safety of panitumumab in the frail elderly patients with WT RAS and WT BRAF [12]. Although 75% of patients received panitumumab as second-line therapy, the median PFS and OS were 6.4 months (95% CI, 4.9–8) and 14.3 months (95% CI, 10.9–17.7), respectively [12].

The efficacy of panitumumab as first-line therapy has not been investigated in patients with WT RAS who are not eligible for intensive chemotherapy. There is no clear definition of frail elderly patients, however, the World Health Organization defined the elderly as individuals aged ≥65 years. Further, the Japanese government has redefined the term “elderly” as those individuals aged ≥75 years [15]. Thus, we will conduct a phase II trial on the efficacy of panitumumab in the frail elderly patients aged ≥76 years or ≥ 65 years who are not eligible for intensive chemotherapy. The results of this trial will affect the treatment strategy of CRC.

## Methods/design

The Osaka Gastrointestinal Cancer Chemotherapy Study Group (OGSG) Protocol Review Committee approved this study protocol on 18 October 2016. Patient enrollment began on February 9, 2017. Approval was obtained from the Institutional Review Board before starting patient accrual at each institution. This trial was registered at the UMIN Clinical Trials Registry as UMIN000024528 on December 1, 2016. The study is being conducted according to the guidelines of the Declaration of Helsinki and the International Conference on Harmonization E6 Good Clinical Practice. The ethical committee or institutional review committee at each site approved the protocol before the initiation of the study. All patients are required to sign a written informed consent.

### Endpoints

#### Primary endpoint

The primary endpoint is to determine the disease control rate (DCR), defined as a proportion of best overall response of complete response (CR), partial response (PR), or stable disease (SD). Response will be assessed based to the Response Evaluation Criteria in Solid Tumors (RECIST) version 1.1 [16].

#### Secondary endpoint

Secondary endpoints include determining OS (time from enrollment until death from any cause), PFS (time from enrollment until documented progressive disease or death from any cause), and response rate. Time to treatment failure and the incidence of grade 3/4 toxicities were also included as secondary endpoints. Adverse events are being graded according to the Common Terminology Criteria for Adverse Events (Japanese edition, JCOG version v4.03).

### Eligibility criteria

#### Inclusion criteria

Patients with histologically confirmed CRC who are not eligible for curative surgical resectionPatients with WT RASPatients with unresectable CRC who have received no previous systemic chemotherapy. The patients who relapsed in ≥6 months from the end of neoadjuvant or adjuvant chemotherapy are also included.Patients aged ≥76 or ≥ 65 years who were not considered eligible for intensive chemotherapy by the treating physician.Measurable disease according to the modified Response Evaluation Criteria In Solid Tumors (mRECIST) criteria (version 1.1).Adequate organ function according to the following laboratory values obtained within 14 days before enrollment: neutrophil count, ≥1500/mm^3^; hemoglobin, ≥9 g/dL; platelet count, ≥10 × 10^4^/mm^3^; aspartate transaminase and alanine aminotransferase, ≤100 IU/L (in the presence of liver metastasis, ≤200 IU/L); total bilirubin, ≤2 mg/dL; creatinine clearance, ≤30 mL/min.Life expectancy ≥90 days from enrollmentWritten informed consent before study-specific screening procedurePatients who did not previously receive treatment with anti-EGFR antibody

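### The renal inclusion criterion sets an upper limit on creatinine clearance (≤30 mL/min) within the adequate organ function item, so as printed it contradicts its own heading

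*Protocol article*

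**What the plan says.** In the protocol article, under Eligibility criteria, Inclusion criteria, one item sets the laboratory requirements for entry. It opens with "Adequate organ function according to the following laboratory values obtained within 14 days before enrollment". The limits then follow in a single list:

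- Hematology: "neutrophil count, ≥1500/mm^3^; hemoglobin, ≥9 g/dL; platelet count, ≥10 × 10^4^/mm^3".
- Transaminases: "aspartate transaminase and alanine aminotransferase, ≤100 IU/L (in the presence of liver metastasis, ≤200 IU/L".
- Bilirubin and renal function: "total bilirubin, ≤2 mg/dL; creatinine clearance, ≤30 mL/min".

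The Exclusion criteria list no renal condition. Creatinine clearance is not mentioned in the Abstract, Treatment, Study design and statistical considerations, or Discussion. The line quoted last is therefore the only renal eligibility rule in the article.

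**The concern.** An organ-function item exists to keep out patients whose function is too poor. For a measure that increases with better function, that calls for a minimum. The renal line sets a maximum instead. A site or reader who takes it at face value would admit patients with low clearance and turn away those with higher clearance.

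Two things are at stake. First, this is an operative entry rule: it decides who may receive the study drug and who counts as ineligible, so an inverted rule bears on patient safety. Second, the criterion describes the population to which the disease control rate and the grade 3/4 toxicity rates will apply. As printed, a reader would conclude that the trial studied only patients with a clearance of 30 mL/min or less, which nothing else in the article suggests was intended.

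**Working it through.** No formula applies, and the article gives no figure to reproduce. The check compares the direction of each limit with the purpose stated in the item's heading.

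**Inputs.** All limits come from the organ-function item under Inclusion criteria. One premise is not in the article: which direction of each measure means better function. This is the ordinary meaning of each test.

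**Step 1. Test for consistency.** A limit fits the heading if, whenever a patient with a given value is admitted, a patient with better function on that measure is admitted too. Higher-is-better measures then need a lower limit, and higher-is-worse measures need an upper limit.

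**Step 2. Apply it to each line.**

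| Measure | Higher value means | Printed limit | Direction that fits the heading | Consistent? |
|---|---|---|---|---|
| Neutrophil count | better | ≥1500/mm³ | lower limit | yes |
| Hemoglobin | better | ≥9 g/dL | lower limit | yes |
| Platelet count | better | ≥10 × 10⁴/mm³ | lower limit | yes |
| AST and ALT | worse | ≤100 IU/L (≤200 with liver metastasis) | upper limit | yes |
| Total bilirubin | worse | ≤2 mg/dL | upper limit | yes |
| Creatinine clearance | better | ≤30 mL/min | lower limit | **no** |

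Five of the six lines fit the heading. The renal line is the only one that does not.

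**Step 3. Read the renal line literally.** A clearance of 30 mL/min or less meets the criterion. A clearance above 30 mL/min fails it. Patients with better renal function are refused and patients with worse renal function are accepted.

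**Step 4. Look for a correction elsewhere.** A renal exclusion criterion, or a restatement of the limit in another section, could show which reading was meant. There is neither.

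**Step 5. Consider a text-conversion fault.** The same sentence shows both ≥ and ≤ in sensible places for the neighboring values, so a systematic conversion fault is unlikely. The source page is not at hand to exclude one for this single character.

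**Step 6. Check whether the statistics depend on it.** Under Study design and statistical considerations, the hypotheses (disease control rate 45% against more than 70%), the power of 0.90, the required 33 patients, the enrollment of 36 and the requirement of more than 22 events are all stated without reference to renal function. None of them changes.

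**The case against.** The strongest reply is that this is a slip in print with no effect on the trial. The article condenses a fuller protocol that was approved on 18 October 2016, and enrollment began on February 9, 2017. The Discussion refers to an August 2018 approval of BRAF testing in the past tense, so the text was finished about 18 months or more into accrual. It cannot have governed the screening of patients who entered before then, and nothing shows that the protocol used at sites carries the same sign. A site would also be unlikely to follow a line that so plainly contradicts its heading.

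Much of this stands. It means that the article gives no ground for assuming that patients were wrongly selected, or that sites need a correction whatever the full protocol says. It does not remove the contradiction in the published criterion. Nor is this a detail left to a fuller document: the article states the rule, and states it against its own heading.

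A reader might infer four stronger points, none of which the article supports:

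- **That the plan tolerates only 3 deviations, so the error would use up the allowance.** The article raises the total from 33 to 36 to account for deviation. The difference, 36 − 33 = 3, is an enrollment margin, not a cap. The article does not say that ineligible patients leave the primary analysis.
- **That nearly every screened patient would be a violation.** No clearance distribution is given for this frail elderly population, so the share above 30 mL/min cannot be stated.
- **That the safety profile would shift through magnesium disturbance.** Hypomagnesemia is named as a toxicity, but the article does not link it to renal clearance.
- **That one character needs changing.** The article does not establish whether the sign, the value or the named measure is at fault.

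**Conclusion.** The point holds as an internal contradiction in an eligibility rule. The renal line is wrong as written: it is the only one of six laboratory limits that runs against the heading it sits under, and nothing else in the article corrects it. Taken literally, it restricts the trial to patients with a creatinine clearance of 30 mL/min or less.

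The conclusion rests on two assumptions: that higher clearance means better renal function, and that the character shown is the one on the published page. The first is the ordinary meaning of the measure. The second is likely, given the correct signs around it, but could not be checked against the page.

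The practical size is open. If the operative protocol is worded consistently with its heading, the harm is limited to a misleading published population description. If it carries the same line, the eligibility of enrolled patients is in question until their screening values are reviewed. The article does not show which case applies, and it does not establish what limit was intended. The sample size and decision rule are unaffected either way.

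**What to change.** 1. Compare the renal line with the item's heading, the full protocol and the criterion actually applied at screening, and settle the direction, the value and the measure together. The trial team must settle the intended limit from its own records; no limit is proposed here.
2. Correct the published text to match.
3. Notify sites only if the operative protocol carries the same error.
4. In that case, check the screening clearance of every enrolled patient against the reconciled criterion before the analysis set is fixed, and record any patient who does not meet it.

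The first two steps cost a document comparison and a correction notice. The last two, if needed, cost a notice to sites and a review of screening values for at most the 36 planned patients. These values should already be on file, since the item requires them within 14 days before enrollment. No redesign and no new sample size calculation are needed.

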#### Exclusion criteria

Uncontrolled diarrheaSymptomatic interstitial pneumonia or pulmonary fibrosisPrevious palliative radiation therapy for bone metastasis or brain metastasis within 2 weeksHistory of other malignancy with a disease-free interval < 1 year (other than curatively treated cutaneous basal cell carcinoma, curatively treated carcinoma in situ of the cervix, and gastroenterological cancer confirmed to be cured by endoscopic mucosal resection)Active infectionsSerious complications: gastrointestinal bleeding, symptomatic heart disease (including unstable angina, myocardial infarction, and heart failure), and uncontrolled diabetes mellitusHistory of serious anaphylaxisRequirement of continuous treatment with systematic steroidsPsychiatric disability that would preclude study compliancePositive for Hepatitis B surface antigenOtherwise determined by the investigator to be unsuitable for participation in the study

### Treatment

Panitumumab 6 mg/kg IV infusion will be administered every 2 weeks. Patients will receive treatment until progressive disease, unacceptable toxicity, patient withdrawal/physician decision, or planned conversion surgery with the intention of curative resection.

After the second cycle, the protocol treatment will be started if skin toxicities (acne, dry skin, nail changes) are ≤ grade 2 and hypomagnesemia is ≤ grade 1 (Table 1) on day 1 of the cycle or the day before the scheduled date. If treatment cannot be started within 28 days, the patients will be withdrawn from the study. If there is grade 3 skin toxicities or hypomagnesemia (Table 2), the dose will be reduced (Table 3).

**Table 1 Tab1:** Criteria for starting treatment after second cycle

	Criteria for starting treatment
Skin toxicities^a^	Grade ≦2
Infusion reaction	Grade≦1
Hypomagnesaemia	Grade ≦2
Nausea vomiting diarrhea	Grade ≦2
Anemia	Hb≧8.0 g/dL
Thrombocytopenia	≧50,000 /m^3^

^a^acne, dry skin, nail changes, etc.

**Table 2 Tab2:** Adverse Events Requiring Dose Reduction

	Grade	The modification from next cycle
Skin toxicities^a^	≧3	Hold dose of treatment and One level dose down
Hypomagnesaemia	≧3	
Pulmonary fibrosis	≧2	Withdrawal from study
Infusion reaction	≧3	Hold dose of treatment

^a^acne, dry skin, nail changes, etc.

**Table 3 Tab3:** Dose reduction levels

Level	Panitumumab
0	6 mg/Kg
-1	4.8 mg/Kg
-2	3.6 mg/Kg

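### The Treatment text and Table 1 set different hypomagnesemia grades for starting a cycle, so a patient at grade 2 gets opposite instructions

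*Protocol article*

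**What the plan says.** The Treatment section of the protocol article gives the rule for starting a cycle twice, once in the running text and once in Table 1.

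- **Text.** It opens: "After the second cycle, the protocol treatment will be started if skin toxicities (acne, dry skin, nail changes) are ≤ grade 2". It then adds the second condition, that "hypomagnesemia is ≤ grade 1 (Table 1) on day 1 of the cycle or the day before the scheduled date". Table 1 is thus cited as the source of the hypomagnesemia condition.
- **Table 1.** Its title is "Criteria for starting treatment after second cycle", and its hypomagnesemia row reads "Hypomagnesaemia Grade ≦2".

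The next sentence of the text sets the consequence of a prolonged hold: "If treatment cannot be started within 28 days, the patients will be withdrawn from the study". The dose-reduction rule follows: "If there is grade 3 skin toxicities or hypomagnesemia (Table 2), the dose will be reduced (Table 3"). Table 2 places the trigger for both toxicities at grade 3 or higher.

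Under Secondary endpoint, the article states: "Time to treatment failure and the incidence of grade 3/4 toxicities were also included as secondary endpoints".

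**The concern.** One criterion has two stated values, and the text names as its source the table that it contradicts. Whoever applies the rule to a patient with grade 2 hypomagnesemia on the assessment day will breach one of the two statements, whether the patient is treated or held.

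The case is foreseeable. The Background names hypomagnesemia, with skin toxicity, as an example of a panitumumab-related toxicity that needs management. The consequence can also be lasting. Under the text, a grade 2 value that does not resolve leads through the 28-day rule to withdrawal. Under the table, the same patient may be treated as scheduled. Three things are exposed to this:

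- the treatment received, and with it the exposure behind the incidence of grade 3/4 toxicities;
- time to treatment failure, a secondary endpoint;
- the monitoring committee's review of protocol compliance, which has no single standard to judge against at grade 2.

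**Working it through.** No sample size, power or error rate enters this point, so no formula applies. The check sets the two statements side by side.

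**Step 1. Is it the same decision?** Yes. The text and the title of Table 1 both concern starting treatment after the second cycle, and the text refers to the table.

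**Step 2. Is the mismatch general or specific?** The text names two toxicities. For skin toxicity, the text and Table 1 agree on grade 2 or lower. Only hypomagnesemia differs.

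**Step 3. Compare grade by grade, with all other start criteria met.**

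| Hypomagnesemia on assessment | Text (grade 1 or lower) | Table 1 (grade 2 or lower) | Agreement |
|---|---|---|---|
| Grade 0–1 | start | start | yes |
| Grade 2 | do not start | start | **no** |
| Grade 3 or higher | do not start | do not start | yes |

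**Step 4. Does anything else settle grade 2?** No. The dose-reduction sentence and Table 2 begin at grade 3, and Table 3 lists only dose levels. No statement gives the text or the table precedence.

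**Step 5. What follows at grade 2?** Under the text, the cycle is held, and the patient is withdrawn if treatment cannot start within 28 days. Under Table 1, the cycle starts.

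**Step 6. How many patients?** The article gives no rate of grade 2 hypomagnesemia, and none for grade 2 that lasts beyond 28 days. The number affected among the planned 36 cannot be computed.

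**The case against.** **The source may be clean.** The article condenses a fuller protocol that is not shown. Enrolment began in February 2017, and the Discussion mentions an approval in August 2018, so the article was written after the trial had opened. Sites would be expected to work from the full protocol, and the mismatch may be a slip in the article alone. This stands in part: different practice between sites is a possibility, not an established fact. But condensing a document explains missing detail. It does not explain two values for one criterion, and the published text contradicts itself either way.

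**The text is shorter than the table.** The paragraph names two toxicities, while Table 1 also covers infusion reaction, gastrointestinal symptoms and blood counts. A reader might count this as a second contradiction. It is not one. The paragraph cites the table, and nothing in it conflicts with those other rows.

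**The primary endpoint.** A reader might infer that the conflict endangers the test of the disease control rate. One patient in 36 is 1/36 = 2.8 percentage points. Against the 45% null, the exact one-sided p-value is 0.075 for 21 of 36 and 0.038 for 22 of 36. The figures are correct, but they do not measure this defect:

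- They would apply to any issue touching one patient.
- Disease control is scored by best response, so a patient with a qualifying response already recorded stays a success after a hold or withdrawal. A change would need grade 2 hypomagnesemia that persists past the limit before any qualifying assessment, in a patient whose best response would otherwise have differed. The article gives no frequency for any of these steps.
- It does not say that a withdrawn patient counts as a failure.
- The statistical section asks for more than 22 events. Read literally, that puts the boundary between 22 and 23, not between 21 and 22.

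**Conclusion.** The contradiction is real and needs correction. Text and table give different hypomagnesemia criteria for the same decision, and nothing in the article resolves them. It is an inconsistency in a stated treatment rule, and nothing suggests that two thresholds were intended.

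Its reach is one grade of one toxicity. At that grade the instructions are opposite, and one of them can end in withdrawal. The plausible effects are on treatment exposure, toxicity, compliance review and time to treatment failure. Their size is unknown. No effect on the disease control rate is shown, and the sample size and decision rule do not depend on this point.

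The case for correction rests on patient safety and consistent treatment, at trivial cost. Whether any patient was handled differently depends on the full protocol, which is not available here.

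**What to change.** 1. Check the paragraph and Table 1 against the full protocol.
2. Reconcile the two to one hypomagnesemia criterion. Which grade applies is for the sponsor's clinical team; this review takes no position on it.
3. If the full protocol has a single value, correct the article.
4. If the full protocol holds the same conflict, amend it, notify the sites, and record which version was applied to patients already treated, so that holds, withdrawals and deviations at grade 2 can be interpreted in the analysis of time to treatment failure and toxicity.

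The cost is a one-line correction or amendment. Only in the last case are a site notice and a look back at treated patients needed as well. The sample size and the primary analysis do not change.

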### Study design and statistical considerations

The aim of the OGSG1602 phase II study is to assess the efficacy of panitumumab as first-line therapy for patients with WT RAS CRC who are not eligible for intensive chemotherapy. Therefore, we decided that the primary endpoint is the DCR and secondary endpoints are PFS, OS, response rate, time to treatment failure, and the incidence of grade 3/4 toxicities. The DCR is assessed by best response. An independent review committee assess efficacy. Based on the AVEX trial and the Spanish phase II study conducted by Sastre et al., the null hypothesis is “DCR is 45%,” and the alternative hypothesis is “DCR is >70%” [10, 11]; this will be assessed using an exact *p*-value of 0.05 and a power of 0.90 based on the Clopper-Pearson method. Thus, the sample size is 33. The total sample size is set to 36 to account for deviation. More than 22 events of DCR are needed for rejecting the null hypothesis. All statistical analyses will be conducted at the OGSG Data Center.

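### Two toxicity rules withdraw patients from the study rather than from protocol treatment, which conflicts with following PFS and OS to progression or death

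*Protocol article*

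**What the plan says.** The Treatment section uses two different terms for stopping. Progression, unacceptable toxicity, a patient or physician decision, and planned conversion surgery are listed as reasons for ending *treatment*. For a cycle that cannot begin in time the consequence is stronger: "If treatment cannot be started within 28 days, the patients will be withdrawn from the study". Table 2 likewise sets withdrawal at study level, not treatment level, for pulmonary fibrosis of grade 2 or worse.

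The Secondary endpoint section defines "PFS (time from enrollment until documented progressive disease or death from any cause" and runs OS from enrollment to death from any cause. It also lists the incidence of grade 3/4 toxicities. It makes no exception for withdrawn patients.

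DCR is "defined as a proportion of best overall response of complete response (CR), partial response (PR), or stable disease (SD"; the article does not name the denominator. The statistical section says "Thus, the sample size is 33", then "The total sample size is set to 36 to account for deviation", and gives the success rule as "More than 22 events of DCR are needed for rejecting the null hypothesis".

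**The concern.** If study withdrawal means what it says, a patient whose toxicity does not resolve within 28 days, or who develops lung toxicity, contributes no later scan, survival status or adverse event. The stated PFS and OS cannot then be observed for that patient and would have to be censored at withdrawal.

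Such censoring is unlikely to be independent of prognosis. These are frail elderly patients leaving because of drug toxicity, and their later course is plausibly worse than that of patients who stay on treatment. PFS and OS would then be biased upwards. In a single-arm trial no comparator shares the bias, and the results will be read against historical figures. Toxicity that worsens or appears after withdrawal would also be missing from the grade 3/4 incidence.

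**Working it through.** **1. The rules set side by side**

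| Event | Consequence in the Treatment section | What the endpoints need |
|---|---|---|
| Progression | Treatment ends | PFS event; survival follow-up for OS |
| Unacceptable toxicity | Treatment ends | Scans to progression; survival follow-up |
| Cycle not startable within 28 days | Leaves the study | Scans to progression; survival follow-up |
| Pulmonary fibrosis, grade 2 or worse (Table 2) | Leaves the study | Scans to progression; survival follow-up |

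The first two rows agree with the endpoints and the last two do not. The 28-day rule directly follows the toxicity criteria for starting a cycle (Table 1), so most patients who meet it will probably do so because of toxicity.

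**2. How far PFS or OS could move**

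The article gives no expected number of withdrawals, so the number k is an assumption. Suppose k of 36 patients are censored at withdrawal times c before a landmark t, and all in truth have the event before t. The Kaplan-Meier estimate S credits each with S(t)/S(c), which is at most 1. The overstatement at t is therefore (1/36) × the sum of S(t)/S(c), and at most k/36:

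- k = 1: 1/36 = 2.8 percentage points
- k = 3: 3/36 = 8.3 points
- k = 6: 6/36 = 16.7 points

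These are upper limits. The bias is smaller if some of these patients stay event-free, and absent if their outlook matches that of the others.

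**3. Whether the primary test is affected**

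Inputs from the statistical section: null DCR 0.45, alternative 0.70, "value of 0.05 and a power of 0.90". Sidedness is not stated.

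- Planned size, one-sided arcsine formula: n = [(1.645 + 1.282) / (2 × (asin√0.70 − asin√0.45))]² = 32.7, so 33. This matches the stated figure. The two-sided version gives 40.1, so 41, which does not. The allowance is 36 − 33 = 3.
- The success rule is a count. Removing uncontrolled patients from the denominator cannot add controlled ones. Under the null, over all 36 enrolled, P(X ≥ 23) = 0.0175 on the literal reading of the rule, and P(X ≥ 22) = 0.0382 if 22 was meant to suffice. Both are below 0.05.
- At 22 controlled, the exact one-sided p is 0.038 with n = 36 and 0.010 with n = 33. Both fall below 0.05.
- The denominator still changes what is reported: 22/36 = 61.1% against 22/33 = 66.7%, with two-sided 95% Clopper-Pearson lower limits of 43.5% and 48.2%.
- With all 36 kept in, a rule of at least 22 has exact one-sided alpha 0.0382 and power 0.908. At least 23 has alpha 0.0175 and power 0.837.

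**The case against.** The best defence is that the withdrawal wording is loose shorthand for stopping protocol treatment. The definitions of PFS and OS contain no censoring at withdrawal, and the full protocol, which is not shown, may say that follow-up continues. This may well be so, and it limits the point to a contradiction to be reconciled. It does not remove it: the same section separately lists reasons that end only treatment, and a site following the text as printed would stop collecting data.

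A reader might go further and infer that these patients drop out of the DCR analysis and that this could reverse the primary conclusion. The arithmetic is tempting: 21/36 gives exact one-sided p = 0.075 and 21/33 gives 0.024. With 3 uncontrolled patients removed under a true DCR of 45%, the rate among the rest is 0.45 × 36/33 = 49.1%, and the chance of at least 21 of 33 is 0.067. The documents do not support this reading:

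- 21 controlled patients fail the stated count at either denominator. The reversal and the 0.067 both need a cut-off reset to 21, which the article nowhere makes.
- The deviations behind the 33-to-36 allowance are undefined and not tied to these withdrawals. The allowance could equally cover patients found ineligible or never treated.
- Progression ends treatment only, so early progressors are not withdrawn under these rules.
- A patient withdrawn after a scan keeps the best response already recorded.
- The analysis set may be defined in the full protocol or analysis plan.

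**Conclusion.** The point holds for follow-up. Two stated toxicity rules end study participation, which contradicts secondary endpoints that run to progression or death. Followed literally, they make censoring plausibly informative in the favourable direction for PFS and OS and may leave later toxicity unrecorded. The size depends on the unknown number withdrawn: at most 2.8 percentage points per patient on a landmark rate, assuming 36 enrolled and every withdrawn patient having the event before the landmark. The direction rests on the assumption that patients stopping for toxicity do worse than those who continue.

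No error in the primary DCR test is shown. Under the fixed count its one-sided type I error over 36 patients stays at 0.0175 or 0.0382. The missing denominator is not a finding in itself, but it should be settled when the withdrawal wording is corrected, because it affects the reported rate and interval. The point should be corrected, at low cost.

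**What to change.** Reconcile the Treatment section and Table 2 with the Secondary endpoint section, without changing when treatment stops. In both places, replace withdrawal from the study with wording such as: *discontinued from protocol treatment; tumour assessment continues until progression, and survival and safety follow-up continue*. Reserve study withdrawal for patients who withdraw consent to follow-up.

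At the same time, state that patients stopped under these two rules stay in the DCR denominator and count as not controlled if they have no CR, PR or SD.

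The cost is continued routine follow-up for a few patients and possibly slightly less favourable PFS, OS and DCR estimates. If the full protocol already provides for continued follow-up, only the wording needs to change.
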